### Standardization of criteria for inclusion, exclusion and discontinuation

Participants shall meet the following criteria.

### Inclusion

Having an age above 18 years for both sexes.Having diagnosis of an accident with bees of the genus *Apis*.Having agreement from the patient or a responsible family member to receive the antivenom.

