**Methods:**

In order to evaluate the safety and neutralizing capacity of a new apilic antivenom, as well as to confirm its lowest effective dose, a clinical protocol was developed to be applied in a multicenter, non-randomized and open phase I/II clinical trial. Twenty participants with more than five stings, aged more than 18 years, of both sexes, who have not previously received the heterologous serum against bee stings, will be included for 24 months. The proposed dose was based on the antivenom neutralizing capacity and the number of stings. Treatment will be administered only in a hospital environment and the participants will be evaluated for a period up to 30 days after discharge for clinical and laboratory follow-up.

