### Design of the *Apis* study

This is a multicenter, non-randomized and open phase I/II clinical trial study to evaluate the safety, determine the pharmacokinetic and proteomic profile, and confirm the lowest antivenom dose, according to the severity of each case. It will include 20 adult individuals, of both sexes, afflicted with multiple stings from Africanized *Apis mellifera* honeybees. The study population will be of the type non-probabilistic by convenience (or accidental) sample, given the low demographic density of the studied phenomenon and the extreme geographic decentralization of this event. The sample size was estimated by considering examples of phase I/II clinical studies proposing to study the safety and neutralizing power and to confirm the minimum required dose of antivenom [12]. Not performing the sample calculation is justified by the fact that the efficacy outcome is not the target at this moment given that there are no data on safety and adequate dose. The study will last 36 months, with 24 months for recruitment.

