### Exclusion

Having had a previous adverse reaction to heterologous serum produced in horses.Being pregnant.Having a chronic disease, including congenital or acquired immunodeficiency.

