### Plan of treatment (specific, adjuvant, symptomatic and complementary)

#### Specific treatment

The *WHO Guideline for the production control and regulation of snake antivenom immunoglobulins* [12] suggests that the protocol prepared for the specific treatment be based on the estimated quantity of venom inoculated by the bee and on the neutralizing capacity of the antivenin. Thus, the authors suggested:Up to 5 stings: specific treatment is not indicated, except for a medical criterion.Between 5 and 200 stings: two vials of apilic antivenom.Between 201 and 600 stings: six vials of apilic antivenom.Above 600 stings: ten vials of apilic antivenom.

After the dose is determined by the attending medical team, the vials must be opened and their content aspirated by means of a syringe. Next, insert all the content into a flask containing 250 mL of normal 0.9% saline solution, previously emptied. This flask containing the antivenom must be connected into a Y formation with another flask containing 250 mL of 0.9% saline. One large-caliber vein of the forearm must be catheterized and these two contents need to be infused in the Y within two hours. All patients must be hospitalized and monitored throughout the infusion by the continuous presence of the hospital staff at the patient’s bedside. The team must also have at their disposal the drugs and equipment necessary for the treatment of mild or severe adverse reactions. Any adverse events and signs and symptoms of possible toxicity must be noted on the patient’s chart.

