### Conduct according to the number of stings and the presence or absence of anaphylactic reaction

#### Up to five stings

Without anaphylactic shock:➢ remove all of the stingers correctly;➢ prescribe hydrocortisone ointment in isolation or associated with 5% menthol;➢ prescribe dextrochlorpheniramine 6 mg orally, every eight hours as needed;➢ apilic antivenom is not indicated.
In the presence of anaphylactic shock:➢ catheterize access of a large-caliber or central vein to hydrate the patient;➢ follow the protocol contained in the symptomatic treatment item;➢ remove all the stingers correctly;➢ apilic antivenom is not indicated.

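### The eligibility list omits the abstract's threshold of more than five stings, and the treatment rules for five or fewer stings contradict each other

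*Protocol article*

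**What the plan says.** **Who may enter.** The abstract's Methods paragraph describes "Twenty participants with more than five stings, aged more than 18 years, of both sexes", and adds that they are people "who have not previously received the heterologous serum against bee stings". The section Design of the *Apis* study is less specific: "It will include 20 adult individuals, of both sexes, afflicted with multiple stings from Africanized" honeybees, with no number.

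The operative list is introduced as one that participants shall meet. Its Inclusion part has three items: age above 18, "Having diagnosis of an accident with bees of the genus" *Apis*, and agreement by the patient or a responsible relative to receive the antivenom. Its Exclusion part also has three: "Having had a previous adverse reaction to heterologous serum produced in horses", pregnancy, and chronic disease including immunodeficiency. No item gives a sting count.

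**What is done at five or fewer stings.** The Specific treatment section states: "Up to 5 stings: specific treatment is not indicated, except for a medical criterion". Its next band is: "Between 5 and 200 stings: two vials of apilic antivenom". The later section headed Up to five stings states, once for patients without anaphylactic shock and once for patients with it, that "apilic antivenom is not indicated".

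**The concern.** Two things do not fit together. First, the list that a site would use to screen patients is wider than the population the abstract describes. Second, for the people who get in through that gap, the article gives two different treatment rules, and at exactly five stings the Specific treatment section disagrees with itself.

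What is at stake is the content of a 20-person trial whose primary objectives are safety and the lowest effective dose. A participant with five or fewer stings leads to one of two outcomes:

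- **Not treated.** The person takes one of the 20 places but adds nothing on the safety or dose of the antivenom. The Observation under Adverse event counts only what occurs after administration.
- **Treated under the exception.** The person receives a horse-derived serum where the conduct section sees no indication. The approval section says that this is the first evaluation of a bee-sting antivenom in a human clinical trial. The Specific treatment section gives neither the criterion nor a dose for such a case.

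**Working it through.** The plan has no figure to reproduce here. The design section says that no sample size calculation was made. The check is a comparison of the passages.

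**Step 1. Eligibility by sting count.**

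| Source | 1 sting | 2 to 5 stings | More than 5 stings |
|---|---|---|---|
| Abstract, Methods | out | out | in |
| Design section (multiple stings) | out | not ruled out | in |
| Inclusion and Exclusion lists | in | in | in |

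The list alone admits any sting count. Adding the design section removes the single sting. Only the abstract removes two to five.

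The criterion on agreement to receive antivenom does not close the gap. It concerns consent and sets no count.

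**Step 2. Treatment rule by sting count.**

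| Stings | Specific treatment section | Conduct section |
|---|---|---|
| Fewer than 5 | not indicated, with a medical exception | not indicated, no exception |
| Exactly 5 | not indicated with exception (first band), and two vials (second band) | not indicated, no exception |

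The rows contain two separate conflicts: exception against no exception for everyone up to five, and two opposite instructions at exactly five. The heading of the next conduct section, Up to 200 stings, states no lower limit of its own.

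**Step 3. What untreated participants would cost (illustration only).** The documents do not say how many people with five or fewer stings might enter. Assume that k of the 20 do so and are not treated, so that n = 20 − k are treated. Two quantities show the loss:

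- exact one-sided 95% upper bound on an adverse event rate when no event is seen: 1 − 0.05^(1/n)
- chance of at least one event if the true rate is 10% (an assumed rate): 1 − 0.90^n

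| k (assumed) | n treated | Upper bound after zero events | Chance of at least one event at 10% |
|---|---|---|---|
| 0 | 20 | 13.9% | 87.8% |
| 2 | 18 | 15.3% | 85.0% |
| 5 | 15 | 18.1% | 79.4% |
| 10 | 10 | 25.9% | 65.1% |

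For example, 1 − 0.05^(1/15) = 18.1% and 1 − 0.90^15 = 79.4%. The values of k span a range and are not forecasts. A small k costs little; a large one would weaken the safety statement clearly.

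**The case against.** The strongest reply is that the intent is plain. The abstract gives the threshold, the design section and the primary objective both speak of multiple stings, and the article condenses a fuller protocol that the ethics and sanitary authorities reviewed. A careful site would probably not enrol someone with three stings. Much of this stands: the gap lies in the list and not in the whole document. But the article prints a list that participants shall meet, and that list disagrees with its own abstract. This is a conflict between stated rules, not a detail left to a fuller document. The design section's wording still leaves two to five stings open.

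A second reply is that the overlap at exactly five is an editorial slip, since the abstract and the conduct section agree on where the line falls. That is fair as to its weight, but the Specific treatment section still gives two instructions for the same patient.

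A reader might also infer more than the documents support:

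- **That a person with a single sting qualifies.** This is true of the list alone. The design section and the primary objective rule it out.
- **That most bee-sting victims would be admitted, because the Background reports up to 90% of cases as asymptomatic or mild.** That figure is clinical severity, not sting count. The Background itself says that the source did not separate single from multiple stings.
- **That each such enrolment shifts a result by 1/20 = 5 percentage points.** This holds for any participant in any 20-person proportion and measures no error. Nor do the documents say that untreated people would enter the safety denominator.
- **That the missing condition on earlier bee antivenom is a serious gap.** The Background calls this the first antivenom for bee stings, so almost no candidate can have received one.

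**Conclusion.** The point holds in a limited form. The operative eligibility list has no sting threshold, although the abstract requires more than five. Read with the design section, people with two to five stings still meet every listed criterion. For five or fewer stings, the Specific treatment and conduct sections conflict on whether any exception exists, and exactly five stings falls under opposite instructions.

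The consequence is either places used without treatment or treatment where the conduct section sees no indication. Its size cannot be estimated from the documents. The illustration above rests on assumed numbers of untreated participants and an assumed 10% event rate, and shows only the direction and possible range of the loss. The textual conflict does not depend on those assumptions.

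The differing conditions on earlier serum (earlier receipt of bee antivenom in the abstract, an earlier adverse reaction to horse serum in the Exclusion list) are a minor point of consistency.

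**What to change.** 1. State in the Inclusion list the same sting threshold as in the abstract, and use it in the design section in place of the unquantified wording.
2. Reconcile the Specific treatment section with the Up to five stings section on whether any exception exists. The sponsor decides which rule stands; this review takes no position on it.
3. In the Specific treatment section, word the first two bands so that exactly five stings falls in only one of them, consistently with the conduct section.
4. As a minor point, bring the abstract's condition on earlier bee antivenom and the Exclusion list into line.

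The cost is a small amendment to the wording, best made before enrolment. It needs no added patients or procedures.

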### Exclusion

Having had a previous adverse reaction to heterologous serum produced in horses.Being pregnant.Having a chronic disease, including congenital or acquired immunodeficiency.

### Discontinuation

Developing anaphylactic shock resistant to the management protocol for reactions of acute hypersensitivities.Withdrawing from the terms of free and informed consent.

### Plan of treatment (specific, adjuvant, symptomatic and complementary)

#### Specific treatment

The *WHO Guideline for the production control and regulation of snake antivenom immunoglobulins* [12] suggests that the protocol prepared for the specific treatment be based on the estimated quantity of venom inoculated by the bee and on the neutralizing capacity of the antivenin. Thus, the authors suggested:Up to 5 stings: specific treatment is not indicated, except for a medical criterion.Between 5 and 200 stings: two vials of apilic antivenom.Between 201 and 600 stings: six vials of apilic antivenom.Above 600 stings: ten vials of apilic antivenom.

After the dose is determined by the attending medical team, the vials must be opened and their content aspirated by means of a syringe. Next, insert all the content into a flask containing 250 mL of normal 0.9% saline solution, previously emptied. This flask containing the antivenom must be connected into a Y formation with another flask containing 250 mL of 0.9% saline. One large-caliber vein of the forearm must be catheterized and these two contents need to be infused in the Y within two hours. All patients must be hospitalized and monitored throughout the infusion by the continuous presence of the hospital staff at the patient’s bedside. The team must also have at their disposal the drugs and equipment necessary for the treatment of mild or severe adverse reactions. Any adverse events and signs and symptoms of possible toxicity must be noted on the patient’s chart.

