### Objectives

Primary objectives: to evaluate the safety of the antivenom including number and severity of acute adverse events, as well as deaths suspected to be related to the intervention; and to confirm the lowest effective dose when faced with different quantities of venom inoculated in patients exposed to multiple stings from Africanized honeybees.Secondary objectives: to correlate the severity of the initial clinical condition with number of stings.Explanatory objectives: to evaluate the antivenom neutralizing power by pharmacokinetic and proteomic studies; and to evaluate the antivenom pharmacokinetics and immunogenicity.

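### The more-than-five-stings limit in the abstract is not carried into the inclusion list, the dose bands or the low-sting exception

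*Protocol article*

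**What the plan says.** The protocol article touches the lower sting limit in five places.

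- **Abstract, Methods.** The population is "Twenty participants with more than five stings, aged more than 18 years, of both sexes".
- **Design of the Apis study; Objectives.** The design section says: "It will include 20 adult individuals, of both sexes, afflicted with multiple stings from Africanized" honeybees. The primary objective refers to "patients exposed to multiple stings from Africanized honeybees". Neither gives a number.
- **Inclusion and Exclusion.** The lists are introduced with "Participants shall meet the following criteria". Inclusion asks for age above 18, agreement to receive the antivenom, and a diagnosis worded "Having diagnosis of an accident with bees of the genus" *Apis*. Exclusion covers an earlier reaction to equine serum, pregnancy and chronic disease. Neither list mentions a sting count.
- **Specific treatment.** For up to five stings, "specific treatment is not indicated, except for a medical criterion". The next line reads "Between 5 and 200 stings: two vials of apilic antivenom". Six vials follow for 201 to 600 stings, and ten above 600.
- **Up to five stings.** Both branches, without and with anaphylactic shock, end with "apilic antivenom is not indicated". No exception is stated.

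**The concern.** These rules decide who enters the trial and who receives serum, and the article describes this as the first human trial of an antivenom against bee stings. The abstract shows the intended population clearly, but the rules a site would apply do not reproduce it.

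Two consequences follow. First, at exactly five stings, two sites reading *Specific treatment* could give nothing or two vials. Second, a site relying on the inclusion list and the exception could enrol and dose a person with two to five stings. *Risks and benefits* lists acute and delayed hypersensitivity to the serum, and the *Conclusions* section uses these reactions, and the possible later need for another equine serum, to justify not testing in healthy volunteers. Someone with very few stings takes on those risks with little venom to neutralize. Such a person would also count towards the primary safety and improvement outcomes, where an outcome free of venom toxicity says little about the dose.

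**Working it through.** The plan gives no figure to reproduce here. The check compares the rules by sting count, tests the bands as integer ranges, and works out the venom load.

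**1. The rules side by side**

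| Stings | Abstract | Inclusion and exclusion lists | *Specific treatment* | *Up to five stings* |
|---|---|---|---|---|
| 1 | out | no bar | no serum, open exception | no serum |
| 2 to 4 | out | no bar | no serum, open exception | no serum |
| 5 | out | no bar | no serum with open exception, **and** two vials | no serum |
| 6 to 200 | in | no bar | two vials | does not apply |

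The reference to multiple stings in the design section and objectives removes a count of one. It does not remove two to five. The enrolment gap is therefore counts 2 to 5, the exception concerns counts 1 to 5, and the overlap concerns count 5 only.

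**2. The bands as ranges**

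As printed: {n ≤ 5}, {5 to 200}, {201 to 600}, {n ≥ 601}.

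- First and second band share {5}.
- Second and third band meet at 200/201, with no overlap and no gap.
- Third and fourth band meet at 600/601, with no overlap and no gap.

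The two upper boundaries are written without overlap, so the lower one looks like a slip. With {6 to 200} as the second band, every count falls in exactly one band.

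**3. Venom load at the low counts**

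Inputs from *Antivenom development and dose proposal*: about 0.1 mg of venom per sting, and 1.25 mg neutralized per mL of antivenom.

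- Two stings: 2 × 0.1 = 0.2 mg; 0.2 / 1.25 = 0.16 mL of antivenom.
- Five stings: 5 × 0.1 = 0.5 mg; 0.5 / 1.25 = 0.4 mL.
- For comparison, the *Background* puts direct toxicity in adults generally above 200 stings: 200 × 0.1 = 20 mg. Five stings carry 0.5 / 20 = 2.5% of that.

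The article does not state the vial volume. Assume 8 mL (the least that lets two vials cover 200 stings: 2 × 8 × 1.25 = 20 mg) to 10 mL (2 × 10 × 1.25 = 25 mg). Two vials then neutralize 20/0.5 = 40 to 25/0.5 = 50 times the venom of five stings. At six stings the range is 20/0.6 = 33 to 25/0.6 = 42. The two ranges are close, so the excess is a feature of the whole lower band. It adds nothing to this point, which is the unsettled choice between no serum and two vials at five.

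**4. Weight of one participant**

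1 / 20 = 5% of each primary proportion.

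**The case against.** The strongest reply is that a careful reader can work out the intent. The abstract says more than five, the first band expressly includes five, and the *Up to five stings* section twice withholds serum, so the second band must start above five. This is the likely intent, and it keeps the overlap small. It does not remove the two-vial line, which still covers five as printed.

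A second reply is that the article condenses a fuller approved protocol. The abstract's other restriction, no earlier serum against bee stings, is also missing from the lists, which suggests abridgement. Agreement to receive antivenom also presupposes that antivenom is indicated, so enrolment at two to five stings would mostly come through the exception. That last point is fair: the two gaps work together. But the article prints the lists as criteria participants must meet, and the abstract is stricter than those lists. This is a conflict between printed rules, not a detail left out.

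A third reply is that the medical criterion means physician discretion, which the article also grants for adjuvant and symptomatic care, and that the attending team determines the dose. On this reading the later section restates the general rule without its exception. Still, no number of vials is printed for this band. The later section also considers anaphylactic shock, the obvious candidate for an exception, and withholds serum there too. The *Background* agrees, limiting treatment of anaphylaxis to general measures and symptomatic drugs. The printed text gives no basis for applying the exception.

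**Conclusion.** The concern holds, and it is minor. The abstract's threshold is absent from the inclusion list, one sting count is assigned to two dosing rules, and an undefined exception appears in one section and not in the other.

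The size is limited. The overlap touches one integer, and the enrolment gap covers counts 2 to 5. The article does not say how many participants might fall there; given the trial's focus on multiple stings, probably few of the 20. The conclusion does not depend on any assumed vial volume. It rests on the printed text alone; the full protocol was not available and may already settle the matter.

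**What to change.** 1. In *Inclusion*, add a criterion of more than five stings, matching the abstract.
2. In *Specific treatment*, start the two-vial band at 6, so that it runs from 6 to 200.
3. In *Specific treatment*, delete the exception for five or fewer stings, so that it agrees with *Up to five stings*. If the sponsor wants to keep it, state it identically in both sections with its criterion and number of vials, and report the safety of anyone treated under it.

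The cost is three short text edits. Every eligible participant then falls in exactly one dosed band.

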#### Adjuvant treatment

The adjuvant treatment aims to maintain the patient and avoid hemodynamic shock, preserve kidney function, diminish cerebral edema and prevent the dysfunctions resulting from hemoglobinuria. Thus, the following is proposed:Replenish volume by hydrating patient vigorously with 0.9% saline, after catheterization of a large-caliber peripheral vein, in order to ensure hemodynamic stability. Always maintain arterial pressure levels above 90 × 60 mmHg.Use vasoactive drugs including dopamine and/or noradrenaline to treat hypotension refractory to the volume, at the discretion of the medical staff.Suspect rhabdomyolysis when the level of creatine phosphokinase (CPK) is above 5,000 U/mL. The presence of dark urine, of oliguria and/or anuria may also denote the presence of rhabdomyolysis. In this case the volume of 0.9% saline to be infused will be 20 mL/kg, running freely, being repeatable up to three times. The objective will be to maintain a urinary volume between 2 and 3 mL/kg/hour. Vigorous hydration must be maintained until CPK reaches levels below 1,000 U/mL.In the presence of refractory anuria or oliguria, require an evaluation from a nephrologist for potential hemodialysis.In the presence of electrolytic disturbances such as alterations in levels of Na^+^, K^+^, Ca^++^ or Mg^++^, these parameters should be closely monitored. Hyperkalemia and hypocalcemia, when present, must be corrected according to the protocols of the referring services.

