**Fig. 1 Fig1:**
[figure not shown]
Temporal distribution of the number of cases reported for Africanized honeybee sting in Brazil between 2000 and 2015 [4]

The physiopathology of this accident is complex due to the interaction between the diverse toxic components of the venom, the potential target organs and the immune response of the victim [5, 6]. Generally, bee stings can present two different outcomes:Anaphylaxis: occurs in individuals allergic to bee venom. In these cases a single sting can cause serious generalized allergic reactions, possibly leading to death. These consequences are not related to the toxicity of the venom due to the small quantity inoculated. Treatment is limited to general measures and the use of symptomatic drugs aiming to control the anaphylaxis [7].Direct toxicity from the venom: occurs when there are a substantial number of stings – generally more than 200 in adults. In this case, the venom volume is sufficient to cause damage to vital organs. Prominent among the toxic components are melittin and phospholipase A_2_, whose presence accounts for more than 60% of the dry weight of the venom. Direct injury to the cardiovascular, muscular, neurological, dermatological, metabolic, hematological, respiratory and renal systems can lead to death [7, 8].

The clinical manifestations resulting from multiple stings are: generalized pain, intense pruritus, flushing, hyperthermia, papules, urticarial plaques, hypotension, tachycardia, headache, nausea, vomiting, abdominal colic, bronchospasms and psychomotor agitation, which may subsequently evolve to a state of torpor, accompanied by respiratory and cardiac failure and, principally, severe renal failure [8–10]. The most common laboratory alterations are: leukocytosis with neutrophilia, hemolysis, thrombocytopenia, disseminated intravascular coagulation, rhabdomyolysis with increase of creatine phosphokinase (CPK), elevation of the enzymes aspartate aminotransferase (AST) and alanine amino transferase (ALT), increase of urea, creatinine and myoglobin in the urine [8–10].

Mortality is elevated at the extremes of age [4]. In children, due to lower body mass, envenomation can be much more severe, since with many stings the concentration of the toxic components is elevated. In the elderly, greater risk involves such preexisting comorbidities as chronic renal, cardiac or respiratory failure. These constitute an important additional risk factor in patients who are victims of multiple stings.

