### Subsidiary laboratory tests

To evaluate the safety parameters, tests will be required on hospitalization days one, two, five and ten, and at follow up (10, 20 and 30 days after hospital discharge) (Table 1).

**Table 1 Tab1:** Laboratory tests requested during hospitalization and follow-up

Procedures	HOSPITALIZATION			FOLLOW-UP		
	Day 1	Day 2	Hospital discharge	Return 1 (R1) (10 days after discharge)	Return 2 (R2) (20 days after discharge)	Return 3 (R3) (30 days after discharge)
Application of FICT	X					
Demographic data	X					
Clinical history	X					
Clinical exam	X	X	X	X	X	X
Concomitant medications	X	X	X	X	X	X
Adverse events	X	X	X	X	X	X
Vital signs	X^a^	X	X	X	X	X
Hemogram	X	X	X	X	X	X
Urine type I	X^b^	X	X	X	X	X
Urea	X	X	X	X	X	X
Creatinine	X	X	X	X	X	X
AST	X	X	X	X	X	X
ALT	X	X	X	X	X	X
Alkaline phosphatase	X	X	X	X	X	X
Gama GT	X	X	X	X	X	X
Bilirubin (direct)	X	X	X	X	X	X
Bilirubin (indirect)	X	X	X	X	X	X
Fasting blood sugar	X	X	X	X	X	X
Cholesterol (total and fractions)	X	X	X	X	X	X
Fibrinogen	X^b^	X	X	X	X	X
C-reactive protein	X^b^	X	X	X	X	X
ESR	X^b^	X	X	X	X	X
PT	X^b^	X	X	X	X	X
APTT	X^b^	X	X	X	X	X
CPK	X^b^	X	X	X	X	X
Albumin	X	X	X	X	X	X
Globulin	X	X	X	X	X	X
Pharmacokinetic profile	X^c^	X	X	X	X	X
Proteomic profile	X^d^	X	X	X	X	X
Pregnancy test	X^e^					

*FICT* free and informed consent term, *AST* aspartate aminotransferase, *ALT* alanine amino transferase, *gama GT*: gamma glutamyl transferase, *CRP* C-reactive protein, *ESR* erythrocyte sedimentation rate, *PT* prothrombin time, *APTT* activated partial thromboplastin time, *CPK* creatine phosphokinase

^a^The vital signs should be taken every 30 min during the infusion and every hour through the first 12 h after the infusion

^b^Collect before and 12 h after termination of the infusion

^c^Evaluate the profile and level of the antibodies IgG and IgM against the antivenom infusion (before and at 2, 6, 12 and 24 h after infusion)

^d^Evaluate the profile of the different heterologous serum proteins in the antivenom (before and at 2, 6, 12 and 24 h after infusion)

^e^In special cases and at the investigator’s discretion this test could be repeated

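### Both CPK limits in the rhabdomyolysis rule are given in U/mL instead of U/L, so as written the laboratory trigger cannot be reached and the stopping criterion is met from the start

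*Protocol article*

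**What the plan says.** The rule stands in the protocol article under Plan of treatment, Adjuvant treatment.

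- Laboratory trigger: "Suspect rhabdomyolysis when the level of creatine phosphokinase (CPK) is above 5,000 U/mL".
- Clinical trigger: "The presence of dark urine, of oliguria and/or anuria may also denote the presence of rhabdomyolysis".
- Action: "In this case the volume of 0.9% saline to be infused will be 20 mL/kg, running freely, being repeatable up to three times".
- Urine target: "The objective will be to maintain a urinary volume between 2 and 3 mL/kg/hour".
- Stopping criterion: "Vigorous hydration must be maintained until CPK reaches levels below 1,000 U/mL".

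The section opens with an instruction that does not depend on CPK: "Replenish volume by hydrating patient vigorously with 0.9% saline".

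Table 1, under Subsidiary laboratory tests, lists CPK without a unit. Its footnote for the Day 1 CPK sample reads "Collect before and 12 h after termination of the infusion". The Background names "rhabdomyolysis with increase of creatine phosphokinase (CPK") among the common laboratory changes after multiple stings, and severe renal failure among the main clinical consequences.

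**The concern.** CPK is routinely reported in U/L. That is general laboratory practice and is not stated in the article. Limits of 5,000 and 1,000 make a sensible start and stop pair in U/L. In U/mL each is 1,000 times higher.

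The error works in opposite directions on the two limits. A start limit set too high means the laboratory result never prompts the rhabdomyolysis bolus. A stop limit set too high means the condition for ending vigorous hydration already holds before treatment begins. The second effect also reaches participants who enter the rule through urinary signs, because CPK is the only stated endpoint for vigorous hydration in that item.

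At stake is supportive care for a central complication of the envenomation. The trial's statistical conclusions do not depend on it.

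**Working it through.** **Inputs from the article (Adjuvant treatment):** start limit above 5,000 U/mL; stop limit below 1,000 U/mL; bolus 20 mL/kg, repeatable up to three times.

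**Assumptions, not in the article:** CPK is reported in U/L; upper limit of normal (ULN) 150 to 300 U/L; CPK in rhabdomyolysis 5,000 to 900,000 U/L; body weight 70 kg.

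The plan derives neither limit, so there is no calculation of its own to reproduce. The check is a unit conversion and a comparison.

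**Step 1. Conversion** (U/L = U/mL × 1,000 mL/L)

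- Start: 5,000 × 1,000 = 5,000,000 U/L
- Stop: 1,000 × 1,000 = 1,000,000 U/L

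**Step 2. Multiples of the assumed ULN**

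| Limit | Read as U/mL | Read as U/L |
|---|---|---|
| Start | 5,000,000/300 to 5,000,000/150 = about 16,700 to 33,300 | 5,000/300 to 5,000/150 = about 17 to 33 |
| Stop | 1,000,000/300 to 1,000,000/150 = about 3,300 to 6,700 | 1,000/300 to 1,000/150 = about 3 to 7 |

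**Step 3. The rule applied to a range of CPK values**

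| CPK (U/L) | Share of written start limit | Share of written stop limit | As written: start? | As written: stop met? | Read as U/L: start? | Read as U/L: stop met? |
|---|---|---|---|---|---|---|
| 5,000 | 0.1% | 0.5% | no | yes | no (not above) | no |
| 20,000 | 0.4% | 2% | no | yes | yes | no |
| 100,000 | 2% | 10% | no | yes | yes | no |
| 500,000 | 10% | 50% | no | yes | yes | no |
| 900,000 | 18% | 90% | no | yes | yes | no |
| 1,000,000 | 20% | 100% | no | no | yes | no |

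The written stop criterion first fails at 1,000,000 U/L. The written start trigger needs more than 5,000,000 U/L.

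**Step 4. When the stop criterion would be met.** Table 1 gives four in-hospital CPK samples: before the infusion, 12 h after it, Day 2 and discharge. For any CPK below 1,000,000 U/L the criterion already holds at the pre-infusion sample. The text above the table instead names hospitalization days one, two, five and ten. The result is the same, because the first sample decides it.

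**Step 5. What depends on the start limit.** One bolus is 20 mL/kg × 70 kg = 1.4 L. If the wording means three boluses in total, that is 60 mL/kg, or 4.2 L. If it means a first bolus plus three repeats, it is 80 mL/kg, or 5.6 L. These are maximum volumes for a participant without urinary signs, in addition to hydration already ordered. They are not an expected shortfall.

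**The case against.** The strongest reply is that nobody would follow the rule literally. A rule that can never start and is always already stopped exposes its own misprint, and requiring CPK to fall below a limit presupposes that it was above it. Clinicians used to U/L would probably read U/L. This is plausible, and it makes a bedside error less likely. It does not make the text right. The article sets out to standardize care, says all centers in the national research network will be invited, and offers its measures to health professionals in other countries. Such a rule should not depend on each reader correcting it silently.

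A second reply is that other instructions protect the patient: saline regardless of CPK, a blood-pressure floor, urinary signs as an alternative trigger, the urine-output target, nephrology referral and dialysis. This stands, and it limits the harm. However, none of these corrects the CPK stopping criterion, and none replaces the laboratory trigger in a participant with raised CPK and no urinary sign. How often that would occur cannot be estimated from the article.

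A third reply is that the article gives no CPK range, so it cannot by itself prove the limits unreachable, and the assumed ceiling of 900,000 U/L lies just under the written stop limit. The dependence on an assumption is real. The stop conclusion requires CPK below 1,000,000 U/L, and the start conclusion has a much wider margin.

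Finally, the plan contains no faulty calculation, so this is better described as a wrong unit than as an arithmetic error. That is fair and changes nothing of substance.

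**Conclusion.** The concern holds. Both CPK limits are wrong as written by a factor of 1,000, and nothing else in the article corrects them. The conversion is certain. That the trigger is out of reach and the stopping criterion is met at the outset rests on the assumed CPK range, and it holds for any value below 1,000,000 U/L. A unit slip is the most likely explanation, since the same numbers in U/L form a workable pair.

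The point concerns patient safety in supportive care and should be fixed. The likely harm is reduced, though not removed, by the other hydration instructions. Sample size, outcome definitions and analysis are untouched.

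**What to change.** Check the limits against the source of the rule. Then change the unit in both sentences of the Adjuvant treatment section: suspect rhabdomyolysis when CPK is above 5,000 U/L, and continue vigorous hydration until it is below 1,000 U/L.

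The cost is two unit replacements. Nothing in the design, outcomes, sample size or analysis has to change.
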